# Rationale and study protocol to evaluate the SunSmart policy intervention: a cluster randomised controlled trial of a primary school-based health promotion program

**DOI:** 10.1186/s12889-015-1371-8

**Published:** 2015-01-31

**Keywords:** Health promoting schools, Skin cancer, Paediatric, Preventive medicine

## Abstract

**Background:**

Previous evaluations of the SunSmart Program have supported the link between a written sun protection policy and improved sun protection behaviours in New South Wales (NSW) primary schools. However these evaluations have relied on self-reported data and research suggests that direct observations are required to better represent schools’ usual sun protective practices.

**Methods/Design:**

Data will be collected in the summer months of 2014, 2015, and 2016 as part of an 18-month cluster-controlled trial in NSW primary schools (n = 20). Researchers will conduct three direct observations to record students’ hat use and teachers’ use of sun protective measures during recess and lunch periods in each school. Researchers will also record the volume of sunscreen that the Year 6 classes in each school utilise over the term. At the conclusion of baseline data collection, five schools will be randomised into an intervention group that will work with researchers to develop a policy-driven intervention to improve sun safety behaviour in NSW primary schools.

**Discussion:**

An initial review of relevant Australian and New Zealand literature suggests that provision of policy support is likely to improve school sun protection practices; however there is no suggested model for this support. This will be the first objective analysis of sun safe behaviours leading to a policy-driven intervention conducted in Australian primary schools since the 1990s, and will inform the future direction of sun safety in our schools.

**Trial registration:**

Australian and New Zealand Clinical Trials Register ACTRN12614000926639 Registered 28^th^ August 2014.

## Background

Australia has among the highest incidence of skin cancer in the world with approximately 750,000 treatments for melanoma and skin cancer every year [1]. Protecting skin from overexposure to ultraviolet (UV) radiation is the simplest and most effective way to reduce the risk of developing melanoma and other skin cancers [2,3]. The World Health Organization (WHO) [4] suggests that school sun protection programs are the key to skin cancer prevention. The New South Wales Department of Education and Communities (NSWDEC) has demonstrated its commitment to sun safety, releasing updated Sun Safety for Students guidelines [5], which strongly encourage each school community to implement a comprehensive Sun Safety Action Plan.

Cancer Council New South Wales (CCNSW) is a not for profit research and advocacy organisation for all forms of cancer within New South Wales (NSW). The SunSmart Program is their flagship skin cancer prevention program, and supports primary schools to develop and implement comprehensive sun protection policies. The program is based on the World Health Organization’s Sun Protection and Health Promoting Schools principles [6] It applies these principles by; a) negotiating a school-endorsed sun protection policy with schools and the systems that govern them, b) providing sun protection education resources, c) advocating for a healthy and sun-safe school environment that include the scheduling of outdoor activities, providing shaded play and recreation areas, encouraging sun protective clothing, providing and encouraging the wearing of sunscreen and encouraging the role modelling of sun-safe behaviours by teachers and other significant adults at schools, and d) encouraging community and family involvement in sun protection behaviour and awareness.

Previous national and state surveys of school sun protection policies and practices demonstrate that being a member of the SunSmart Program improves sun protection practices in primary schools [7,8]. The national survey of Sun Protection Policy and Practice in Primary Schools demonstrated an association between a written sun protection policy and more effective sun protection practices [8]. However survey results also demonstrate there are opportunities to embed sun protection practices more broadly in primary schools; in particular students’ use of sun-safe hats and sunscreen, and teacher role modelling of positive sun protection practices [8].

A review of relevant Australian and New Zealand literature suggests that provision of policy support is likely to improve school sun protection practices [9,10]. Change agents (project champions like teachers) are suggested as one potential approach for improved policy implementation [11,12]. Furthermore, any policy intervention must consider the nuance and idiosyncrasies of the school and the communities they serve. Given the complexity of the school setting, intervention strategies will need to be innovative and consider issues of design and measurement in dealing with school-based samples.

In 2014 more than three-quarters of NSW primary schools are signatories to the SunSmart Program [13]. Previous evaluations of school sun protection policies have stated the data supporting the link between sun-protection policies and observations of sun protective behaviour at primary schools are lacking [14]. This evaluation by Turner and colleagues also called for research involving independent assessment of policies and direct unannounced observations of behaviour to better represent usual sun protective practices (rather than self-reported data). This study seeks to build on the body of knowledge regarding sun protection behaviours in primary schools. The study will use a novel application of an existing objective observational tool to collect data on key sun-safe practices in schools that are members of the SunSmart Program, and develop and evaluate practical strategies to support schools in improving their sun protection policy.

## Methods/Design

### Study design

The SunSmart Evaluation and Policy Intervention study is an 18-month primary school-based intervention and will be evaluated using a cluster randomised controlled trial. Ethics approval has been sought and obtained from an Australian University Human Ethics Committee (HREC 2014/062) and the New South Wales Department of Education and Communities (SERAP: 2014148). The SunSmart Evaluation and Policy Intervention study is registered with the Australian and New Zealand Clinical Trials Registry (ACTRN12614000926639). The study protocol was also reviewed internally by the research committees of the funding agencies.

Following the initial recruitment processes, researchers will conduct baseline assessments at participating schools. The design, conduct and reporting of this study will adhere to the Consolidation Standards of Reporting Trials (CONSORT) guidelines for a cluster randomised controlled trial [15]. Principals, teachers and parents will provide written informed consent.

### Sample size calculation

Power calculations were conducted to determine the sample size and number of observations required to detect changes in the outcome of students wearing sun protective headwear in a cluster design. Calculations assumed baseline-posttest expected effect size gains of *d* = 0.4/r = 0.19 and were based on 80% power, with alpha levels set at p < 0.05. Using the standard deviation (SD) of change of SD = .5, it was calculated that the study required 50 observations within the intervention and control groups would provide adequate power to detect a between group difference of *d* = 0.4 across the school day.

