### Recruitment and study participants

To be eligible to participate in the study, schools must be government primary schools and be a current signatory to the SunSmart Program in the Greater Western Sydney Region, NSW, Australia (Approx 33.75 deg S, 150.70 deg E).

All eligible schools (n = 167) will be sent an initial email with an invitation to participate in the study. CCNSW and NSWDEC will also identify a short-list of schools that may be receptive to participating in the study (n = 40). Schools that respond to the initial email and the short-listed schools will be pooled and receive a follow up call in random order from the project researchers to ascertain whether they would like to participate in the study. The first twenty schools that demonstrate interest will then be recruited into the study.

Randomisation into intervention and control group will occur after baseline assessments. A simple computer algorithm will be used to randomly allocate schools to either control (n = 15) or the treatment (n = 5) conditions by an independent researcher not involved in the study. This method will ensure all schools have the same likelihood of allocation into one of the two study arms. Trained research assistants and project researchers will conduct all assessments and perform focus groups and interviews. All researchers will complete training sessions prior to assessment to maintain consistency and where possible, the same assessors will be used at baseline, post-test and follow-up. Figure 1 shows the flow of participants through the study.

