### Wearing of headwear and prevailing environmental conditions

The primary outcome will be children’s wearing of a sun protective headwear during break periods of the school day (i.e. recess and lunch). Currently no direct observation instruments to record sun-safe behaviours of children in school settings exist. However several direct observation tools of physical activity do exist, and one of these will be adapted to capture sun-safe behaviour data in children. The System for Observing Play and Recreation in Communities (SOPARC) is based on momentary time sampling techniques in which systematic and periodic scans of individuals and contextual factors within predetermined target areas are made [20]. iPad tablets (Apple Inc, USA) installed with the iSOPARC Application Version 1.75 (CIAFEL, Portugal: http://ciafel.fade.up.pt) will be used to provide an objective measure of the wearing of hats by children during recess and lunch.

During a scan each subject is electronically coded and identified by; sex (male or female), intensity of activity (Sedentary, Walking, or Very Active), and whether they are a Child, Teen, Adult or Senior. For this study, given all the subjects will be children, the third battery of coding (Child, Teen, Adult or Senior) will be changed to detect whether the student is Unprotected (no hat), Partially-Protected (wearing a baseball cap), Fully-Protected (wearing a 360 degree brim; broad-brimmed or bucket hat) or Fully-Protected (wearing a peak cap with back flap; legionnaire hat).

Separate scans are made for females and males, and simultaneous entries are also made for time of day, temperature, UV radiation level, area accessibility, area usability and presence of supervision. Each observation is conducted twice during the recess and lunch breaks for both females and males. This results in each school having 24 observations conducted at each data collection period (i.e. baseline, post-test and follow-up).

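### The stated inputs do not give 50 observations per group for a between-group d = 0.4, and the calculation shown makes no allowance for clustering

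*Protocol article*

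**What the plan says.** The Sample size calculation section concerns "changes in the outcome of students wearing sun protective headwear in a cluster design". It opens on a within-group footing ("Calculations assumed baseline-posttest expected effect size gains of" d = 0.4, also given as r = 0.19) and says the calculations "were based on 80% power, with alpha levels set at p < 0.05". It then brings in a spread ("Using the standard deviation (SD) of change of SD = .5") and concludes that the study "required 50 observations within the intervention and control groups would provide adequate power to detect a between group difference of" d = 0.4.

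The design itself is set elsewhere. Recruitment and study participants will "randomly allocate schools to either control (n = 15) or the treatment (n = 5) conditions". The headwear outcome section says: "This results in each school having 24 observations conducted at each data collection period". Statistical methods plans linear mixed models with treatment, time (three waves) and their interaction, adjusted for clustering and for several covariates.

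**The concern.** The paragraph moves from a baseline-to-post-test gain to a between-group difference while keeping the same 0.4. A sample size that suffices for the first is about half of what each group needs for the second. It also names a cluster design without showing an ICC, a design effect, the number of schools, school-level degrees of freedom or the 5:15 allocation. Observations in one school share its hat policy, staff and grounds, so they cannot be taken as independent.

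This is the article's only power statement for the primary outcome. If its 80% is taken at face value, a null result from five intervention schools could be read as evidence that policy support does not work, when the power actually available was never established.

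**Working it through.** **Inputs from the article.** d = 0.4; r = 0.19; SD of change 0.5; power 80%; alpha 0.05 (sidedness not stated, two-sided taken); 50 observations; 5 v 15 schools; 24 observations per school per wave.

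**Which d is meant.** For two equal groups r = d/√(d² + 4) = 0.4/√4.16 = 0.196. The quoted r therefore fits a standardised two-group difference.

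**Trying to reproduce 50 for a between-group d = 0.4.** n per group = 2(1.960 + 0.842)²/d² = 2 × 7.849/0.16 = 98.1, so 99; the t-based value is 99.1, so 100.

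| Reading of the 50 | Power at d = 0.4 |
|---|---|
| 50 per group, two-sided | 50.8% (t), 51.6% (normal) |
| 50 per group, one-sided | 63.9% (needs 78 per group) |
| 50 in total, 25 per group | 28.3% (t), 29.3% (normal) |

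The figure is not reproduced under any of these.

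**Where 50 does arise.**
- One-group before-after change at d = 0.4: n = 7.849/0.16 = 49.1, so 50 (t-based 51.0; power at 50 is 79.2%).
- Raw difference 0.4 over SD 0.5, so d = 0.8: n = 2 × 7.849/0.64 = 24.5, so 25 per group and 50 in total (t-based 25.5 per group). On this reading, 50 per group would have about 98% unclustered power.
- Baseline-adjusted comparison at d = 0.4: 51 per group if the baseline correlation is 0.7, a value the article does not give.

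**Can clustering be hidden in the 50?** Not at d = 0.4. Fifty is already below the unclustered 99, and a design effect above 1 only raises the requirement.

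**Power of the planned design, single wave.** 5 × 24 = 120 v 15 × 24 = 360 observations. Design effect DE = 1 + 23 × ICC; SE = √[DE × (1/120 + 1/360)] in SD units; noncentral t with 20 − 2 = 18 df and noncentrality 0.4/SE. At ICC 0.05, for example, DE = 2.15, SE = 0.155 and the noncentrality is 2.59. The ICCs are assumptions, because the article gives none.

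| ICC | DE | Power at d = 0.4 |
|---|---|---|
| 0 | 1.00 | 95% |
| 0.01 | 1.23 | 90% |
| 0.028 | 1.64 | 80% |
| 0.05 | 2.15 | 69% |
| 0.10 | 3.30 | 51% |
| 0.20 | 5.60 | 33% |

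**Credit for baseline.** Multiply the variance by (1 − ρ²), where ρ is an assumed baseline-to-post-test correlation of school means, and use 17 df.

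| ICC | ρ = 0 (18 df) | ρ = 0.5 | ρ = 0.7 |
|---|---|---|---|
| 0.05 | 69% | 80% | 93% |
| 0.10 | 51% | 62% | 79% |
| 0.20 | 33% | 42% | 56% |

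This gain is not available if 0.4 is already standardised on the SD of change, a point the article leaves open.

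**The case against.** **The trial collects far more than 50 observations.** This stands. It plans 120 v 360 per wave, against an unclustered need of 66 v 197 at 3:1. A reader might infer that the trial has only 51% power, or that it could not detect the planned effect. The article supports neither: 51% describes the stated calculation, and the design reaches 80% if the ICC is about 0.028 or less, or at a higher ICC if baseline adjustment is strong.

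**The planned analysis is richer than a single-wave comparison.** This also stands. The mixed model uses three waves, a group-by-time term and covariates. A reader might turn the single-wave table into a fixed detectable difference (0.46, 0.57 and 0.74 SD at ICC 0.05, 0.10 and 0.20). Those values rest on assumed ICCs and a simpler analysis, so they are illustrative and should not be printed as the trial's detectable difference.

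**0.4 may be a raw difference over SD 0.5.** Then 50 per group would be ample and would leave room for a design effect of about 2. But that is d = 0.8, which conflicts with the stated d = 0.4 and r = 0.19, and no such inflation is mentioned.

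**Twenty-four may not count both Target Areas.** This is unclear. At 48 per school, single-wave power would be 79% at ICC 0.05 and 57% at 0.10, so the dependence on the ICC remains.

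**An article may leave the ICC to the full protocol.** Taken alone, its absence would be no finding. Here, however, the article prints inputs and a conclusion, and the conclusion does not follow from them.

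**Conclusion.** The stated sample size is wrong as written. For a standardised between-group d of 0.4 at two-sided alpha 0.05, 80% power needs about 100 observations per group before any clustering, twice the stated 50. One-sided testing does not rescue it, and the readings that do give 50 either change the target or need a correlation that is not stated. At d = 0.4 the figure cannot include an inflation for clustering.

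What follows for the trial is narrower. Whether it has 80% power at d = 0.4 is undetermined and depends on an unstated ICC, on the baseline correlation and on which SD the 0.4 refers to. The arithmetic on the 50 rests only on the article's inputs and the two-sided reading. The design-level powers also assume the ICC values, 24 observations per school, equal variances and a comparison of school means.

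**What to change.** Rewrite the Sample size calculation paragraph:

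1. State whether 0.4 is standardised or raw, and on which SD (cross-sectional or change).
2. Replace the 50-observation claim with the power, or the detectable difference, for the group-by-time contrast in the planned mixed model. Use 5 v 15 schools, the actual number of observations per school (saying whether 24 counts both Target Areas), school-level degrees of freedom, and an explicit range of ICC and baseline correlation.
3. Estimate the ICC from the baseline data and report it.
4. State that 80% power at d = 0.4 holds only if the ICC is small or baseline adjustment is strong.

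The cost is one paragraph and one estimate from data already being collected. No extra schools are needed. The downside is a less favourable stated power.

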### Recruitment and study participants

To be eligible to participate in the study, schools must be government primary schools and be a current signatory to the SunSmart Program in the Greater Western Sydney Region, NSW, Australia (Approx 33.75 deg S, 150.70 deg E).

All eligible schools (n = 167) will be sent an initial email with an invitation to participate in the study. CCNSW and NSWDEC will also identify a short-list of schools that may be receptive to participating in the study (n = 40). Schools that respond to the initial email and the short-listed schools will be pooled and receive a follow up call in random order from the project researchers to ascertain whether they would like to participate in the study. The first twenty schools that demonstrate interest will then be recruited into the study.

Randomisation into intervention and control group will occur after baseline assessments. A simple computer algorithm will be used to randomly allocate schools to either control (n = 15) or the treatment (n = 5) conditions by an independent researcher not involved in the study. This method will ensure all schools have the same likelihood of allocation into one of the two study arms. Trained research assistants and project researchers will conduct all assessments and perform focus groups and interviews. All researchers will complete training sessions prior to assessment to maintain consistency and where possible, the same assessors will be used at baseline, post-test and follow-up. Figure 1 shows the flow of participants through the study.

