### Outcomes

Evaluation of the SunSmart Policy Intervention will involve a variety of instruments to report on sun protection behaviours that occur in primary schools. Trained research assistants who will be blind to the control or intervention allocation of the schools will conduct all assessments. All sun protection behaviour practices will be measured at baseline, post-test (12 months), and follow-up (15 months).

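### The 5 v 15 allocation takes place after baseline but does not use the schools' baseline hat data, giving up a cheap gain in balance and precision

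*Protocol article*

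**What the plan says.** Recruitment and study participants sets the number of schools ("The first twenty schools that demonstrate interest will then be recruited into the study"), the timing ("Randomisation into intervention and control group will occur after baseline assessments") and the method: "A simple computer algorithm will be used to randomly allocate schools to either control" (15 schools) or treatment (5 schools), with the draw made by a researcher from outside the study. The abstract gives the same order: "At the conclusion of baseline data collection, five schools will be randomised into an intervention group".

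The only property claimed for the method is this: "This method will ensure all schools have the same likelihood of allocation into one of the two study arms". No stratification, matching, minimisation or balance constraint is described.

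Under Wearing of headwear and prevailing environmental conditions the article states: "The primary outcome will be children’s wearing of a sun protective headwear during break periods of the school day". The Outcomes section has it measured at baseline, 12 months and 15 months.

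Statistical methods specifies linear mixed models with treatment, time (baseline being one level of time) and their interaction. The covariates are sex, temperature/UV, time of day, type of period and target-area conditions. A school's baseline hat level is not among them.

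**The concern.** Baseline observation of all 20 schools is finished before any school is allocated, so the best available predictor of later hat wearing is in hand. The stated procedure does not use it. In an intervention arm of five, each school carries one fifth of the arm mean, so one or two unusual schools can move it noticeably.

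At stake are the precision of the treatment estimate and how far readers will trust it if the arms visibly start apart. An analysis plan written later can adjust for an imbalance but cannot undo the draw, so the matter has to be settled at the design stage.

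**Working it through.** The article gives no figure for baseline balance, so there is none to reproduce. The check derives one from the stated design.

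**Inputs from the article:** 20 schools; 5 intervention and 15 control; allocation after baseline; primary outcome observed at baseline; group-by-time analysis with baseline as a level of time.

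**Assumed, because the article does not give them:** the between-school SD of baseline hat wearing (σ), roughly normal school values, and the baseline to follow-up correlation of school means (ρ).

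**Step 1. Spread of the baseline arm difference.** SE = σ × √(1/5 + 1/15) = σ × √0.2667 = 0.516σ. For comparison, 10 v 10 would give σ × √(1/10 + 1/10) = 0.447σ.

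**Step 2. Chance of a gap larger than t school SDs.** P = 2 × [1 − Φ(t / 0.516)].

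| Gap over | Formula | Enumeration |
|---|---|---|
| 0.25 SD | 62.8% | 62.8% |
| 0.4 SD | 43.9% | 43.8% |
| 0.5 SD | 33.3% | 33.2% |
| 0.75 SD | 14.6% | not run |
| 1 SD | 5.3% | 5.2% |

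The last column lists all C(20,5) = 15,504 possible allocations for each of 400 simulated sets of 20 school values and averages the results.

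**Step 3. In percentage points, over a range of σ.** The chance of a gap over 10 points is 2 × [1 − Φ(10 / (0.516σ))].

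| Assumed σ (points) | SE (points) | Chance of gap over 10 points |
|---|---|---|
| 10 | 5.2 | 5% |
| 15 | 7.7 | 20% |
| 20 | 10.3 | 33% |
| 25 | 12.9 | 44% |

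**Step 4. What reaches the planned contrast.** The group-by-time term compares changes. Take equal school SDs at both times, no treatment effect and a baseline gap g. The expected later gap is ρg, so the difference in change is ρg − g = −(1 − ρ)g. For g = 0.5 SD its size is:

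- ρ = 0.3: 0.7 × 0.5 = 0.35 SD
- ρ = 0.5: 0.5 × 0.5 = 0.25 SD
- ρ = 0.7: 0.3 × 0.5 = 0.15 SD
- ρ = 0.9: 0.1 × 0.5 = 0.05 SD

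**Step 5. The same design with ranked strata.** Rank the 20 schools on baseline hat wearing, cut them into five strata of four, and draw one intervention school from each. This leaves 4^5 = 1,024 allocations, still 5 v 15. Enumerated on the same 400 simulated sets:

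| Gap over | As planned | Ranked strata |
|---|---|---|
| 0.25 SD | 63% | 16% |
| 0.4 SD | 44% | 3% |
| 0.5 SD | 33% | 0.9% |
| 1 SD | 5% | about 0% |

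**The case against.** The strongest defence is that nothing here is invalid. An independent researcher makes a random draw, and the treatment estimate is unbiased over all draws. The planned model compares changes from baseline, so the raw gaps in Steps 2 and 3 are subtracted out and are not errors in the treatment effect. The residual in Step 4 falls in either direction with equal chance and is part of ordinary sampling error. All of this stands, and it limits the point to precision and credibility. It does not remove the point, because the residual is avoidable noise in a trial with five intervention schools and the data to reduce it are already collected.

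It is also fair that school-SD units do not show whether a gap matters in practice; Step 3 therefore gives a range. Nor should these gaps be set against the d = 0.4 in the sample size section, which is not in school-SD units.

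A reader might infer more than the article supports:

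- **That allocation is wholly unrestricted.** Arm totals are fixed at 5 and 15. Independent draws at 25% would give exactly five intervention schools only about 20% of the time. What is missing is any use of baseline characteristics.
- **That the equal-likelihood sentence is wrong.** Each school has the same 5/20 = 25% chance of intervention. The sentence is true as written and makes no claim about balance.
- **That a high-starting intervention arm would hit a ceiling.** The article gives no baseline hat prevalence, and its Background names students' hat use as an area with room to improve.
- **That regression to the mean would bias the result.** It can distort a single draw, as Step 4 shows, but under random allocation it favours neither arm.

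**Conclusion.** The point holds as a worthwhile design improvement; it does not show an invalid allocation. Under the stated method, about one draw in three leaves the arms more than 0.5 between-school SD apart on baseline hat wearing, and about one in twenty more than 1 SD apart. These chances follow from 5 v 15 and approximate normality.

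The size in percentage points depends on a between-school SD that the article does not give. The part that survives into the change contrast depends on an assumed school-level correlation: for a 0.5 SD gap it runs from 0.35 SD at a correlation of 0.3 down to 0.05 SD at 0.9. If schools' hat wearing is very stable over time, the gain for the planned contrast is therefore small; if it is not, the gain is appreciable.

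**What to change.** Replace the simple draw with a stratified one made by the same independent researcher. Once baseline is complete, rank the 20 schools on baseline hat-wearing proportion, form five strata of four, and randomly select one school in each stratum for intervention. This keeps 5 v 15, and each school's chance stays at 1/4 = 25%, so the article's equal-likelihood statement remains true.

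Strata are preferable here to keeping only the best-balanced tenth of all 15,504 allocations. In simulated school sets balanced on hat use and enrolment, that rule made schools' chances of intervention unequal, on average from about 17% to 29%, which would contradict the statement.

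Carry the school's baseline hat level, or the stratum, in the analysis model. While baseline remains a level of time, a main effect alone shifts every time point together and hardly touches the change contrast. Either make baseline a covariate with post-test and follow-up as the outcomes, or cross the stratum with time.

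The cost is a short script before allocation and a few degrees of freedom. Two arms of 20 schools leave 20 − 2 = 18 at school level; a baseline covariate takes 1 of these (17 left), and five strata take 4 (14 left). No extra school, visit or measurement is needed.
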